## Discussion

This study will provide a deeper understanding of sport as a tool for the personal development of socially vulnerable youth. This study has four research aims: (1) to provide insights on the causal relationship between sport participation and life prospects of socially vulnerable youth, and the underlying mechanism by which sport can improve life prospects; (2) to explore the life experiences in the sport context of socially vulnerable youth that can lead to skill development; (3) to examine the social conditions that may strengthen the positive effect of sport on life prospects, and; (4) to provide insights into the organisational context of successful sport inclusion in youth care practices by exploring elements of successful and enduring partnerships between professional and voluntary organisations.

Sport participation is linked to many positive outcomes and is often applied as a tool for positive youth development. Coakley argues that these claims of positive youth development through sport participation are voiced by ‘sport evangelist’ and are based on wishful thinking and personal testimonials [63]. As a consequence, Coakley claims that more critical research and theory is needed that could support policy-makers and program officials in making decisions about sport for positive youth development [63]. In a similar way, Coalter states: *“What is required is a developmental approach based on the de-reification of ‘sport’, and a concentration on understanding the social processes and mechanisms that might lead to desired outcomes for some participants or some organisations in certain circumstances* (p. 311)”. The current study adopts such a critical approach to sport for positive youth development by reviewing the phenomenon from different theoretical perspectives, with different methodological approaches and by examining different elements of the ‘black box’.

### Strengths and limitations

There has been a large amount of research investigating the positive outcomes of sport participation. These studies often draw conclusions on the association between sport and the studied outcome based on cross-sectional data. This current study aims to contribute to these findings by investigating the outcomes over a longer period of time (1.5 year) and to report on the causal effects of sport participation by comparing the outcomes of the experimental and the control group. We will explore the life experiences of socially vulnerable youth in the sport context which will allow us to draw a more comprehensive and rich picture of sport-based activities for socially vulnerable youth. In addition, the social conditions and elements of successful partnerships are studied to guide future initiatives of youth care organisations and local sport clubs to use sport as a tool for personal development. The mixed methods design of this study provides insights on the processes occurring in the black box of sport participation that may contribute to the personal development of socially vulnerable youth.

Most studies investigating the factors that influence the performance of the partnership operationalise this performance as the perceived performance by the participants. To explore this relationship for partnerships between youth care organisations and local sport clubs (research aim 4), we use a similar approach. As this part of our study takes place in the same context as the study activities to address research question 1–3, we will also be able to add objective measurements of the partnership’s performance such as the number of youngsters guided to local sport clubs and the presence of beneficial social conditions at local sport clubs.

This study has several limitations. First of all, the quantitative part of this study has a non-equivalent control group design. The training and support given by the Care Sport Connector (CSC) is organised on a regional level, making randomisation at the individual level of the youngsters impossible. This means that the study may be subject to selection-bias if the youngsters differ on baseline characteristics between the control and the experimental groups. Secondly, due to the voluntary nature of sport participation as part of the treatment plan it is likely that the youngsters who join a sport club differ significantly on certain characteristics from the youngsters that choose not to join. This may distort the effect measurement of sport participation on life prospects, self-regulatory skills and SOC. A third limitation concerns the fact that the intervention is executed on the level of the CSC. The effect of the intervention needs to percolate to the level of the health care professionals and the youngsters, which may reduce the effect of the intervention on the outcome measures. A large sample size is needed to measure changes in life prospects of the youngsters. Fourthly, increasing the sport participation of the youngsters in the experimental groups of the Rotterdam youth care organisation is a big challenge. These youngsters are having difficulties in one or more life domains (e.g. family, school or work) and as such are not necessarily focused on engaging in sports in their leisure time. In order to be able to find significant effects of a small size, we need a large sample. Especially the administration of the third questionnaire, when the youngsters have often left the youth care organisation, will be time-consuming for the researchers. Incentives for completion of all three questionnaires are introduced to increase response rates.

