## Methods/Design

### Study design

Quantitative and qualitative data for this study will be collected in several phases and for different purposes (see for an overview Figure 2). All the data is gathered in Rotterdam where an intervention is implemented in a youth care organisation that aims to increase the sport participation of socially vulnerable youth. The intervention will be implemented in three regions of the Rotterdam youth care organisation, two regions are in the control group where no intervention activities take place. As randomisation of the regions is not possible, the regions for the experimental and control condition are selected in such a way that the baseline characteristics of the youngsters are as similar as possible (i.e. a non-equivalent control group design). In addition, to avoid contamination, the experimental groups and the control groups are not located in adjacent regions. After describing the intervention into more detail, the data collection methods are discussed per study aim.

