Training of the youth care professionals by the CSC will exist of various activities, such as interactive workshops, individual face-to-face sessions, and provision of written (online) information. Various topics will be discussed during these events that are relevant for the youth care professionals, for example focusing on practical barriers that they may encounter when guiding their youngsters to local sport organisations (such as money constraints, ethical issues and lack of parental support). These topics were selected after conducting several interviews with youth care professionals discussing their view of the inclusion of sport in youth care practices. During the intervention, additional events may be organised that match the needs of the youth care professionals and the CSC. As such, the training of the youth care professionals can be seen as coaching-on-the-job and the activities can be adapted to individual needs. All activities that take place will be carefully monitored and recorded, so that in the end a precise description of the actual intervention can be given. The activities of the CSC will continue after the end of this study and will be expanded to other regions of the Rotterdam youth care organisation as well.

Within the experimental regions, specific attention is also paid to the socio-pedagogical climate at the local sport clubs. A pedagogue is employed in the experimental regions to support the local sports clubs in their efforts to create a positive learning environment for all children. Several elements of the socio-pedagogical climate receive specific attention such as the setting and maintenance of basic rules at the sport clubs, improving the pedagogical qualities of the trainers and increasing the involvement of parents at the sport club. Similarly to the activities conducted by the CSC, the activities of the pedagogue are documented during the intervention to be able to provide a clear description at the end of the project.

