### Study aim 1: effect of sport participation on life prospects

The first study aim focuses on the causal effect of sport participation on the life prospects of socially vulnerable youth and the underlying mechanisms. More specifically, the following hypotheses were formulated:

1. Sport participation during the care program of socially vulnerable youth leads to improved life prospects as measured in: (a.) school level and performance; (b.) work attendance and performance; (c.) subjective health; (d.) well-being, and; (e.) future outlook.

2. Sport participation leads to enhanced self-regulation skills (i.e. planning, self-monitoring, effort and reflection).

3. Sport participation leads to improved SOC-levels.

4. The positive effect of sport participation on life prospects is mediated by self-regulation skills.

5. The positive effect of sport participation, via self-regulation skills, on life prospects is moderated by SOC.

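### The regional comparison estimates the effect of a care-sport package, not the causal effect of sport participation claimed for it

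*Protocol article*

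**What the plan says.** In the Methods/Design section on study aim 1, the exposure in the first three hypotheses is the youngster's own sport participation:

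- Hypothesis 1: "Sport participation during the care program of socially vulnerable youth leads to improved life prospects as measured in" five listed domains.
- Hypothesis 2: "Sport participation leads to enhanced self-regulation skills".
- Hypothesis 3: "Sport participation leads to improved SOC-levels".

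Under Strengths and limitations, the article says that it will "report on the causal effects of sport participation by comparing the outcomes of the experimental and the control group".

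Under Study design, the arms are whole regions: "The intervention will be implemented in three regions of the Rotterdam youth care organisation, two regions are in the control group". They were not allocated by chance ("As randomisation of the regions is not possible").

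Under Intervention, the experimental regions receive a Care Sport Connector and youth care professionals trained to bring sport into care and guide youngsters to clubs. In addition, "A pedagogue is employed in the experimental regions to support the local sports clubs". Higher sport participation is described there as what the authors expect to follow.

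On self-selection, the limitations say that "it is likely that the youngsters who join a sport club differ significantly on certain characteristics from the youngsters that choose not to join". They also mention possible baseline differences between the arms, and a weakening of the effect as it passes from the connector through the professionals to the youngsters.

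**The concern.** The exposure in the hypotheses and the contrast named to establish their causal effect are different things. Each arm can contain youngsters who play sport and youngsters who do not: participation is voluntary, and Table 1 records it already at T0. The package can also act on youngsters without changing whether they play.

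The results are meant to guide the use of sport in youth care. A positive regional difference could come from the club pedagogue or from closer guidance by professionals, yet be reported as a benefit of sport. A null difference could come from low uptake, yet be reported as sport having no effect.

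**Working it through.** **The plan's own figures.** These are not at fault. A test with 2 numerator degrees of freedom, f = 0.20, N = 244 and noncentrality 244 × 0.20² = 9.76 has power 0.8002 at 5%. The article does not say which G*Power option was used. Baseline number: 244 / (0.80 × 0.70) = 435.7, so 436. The point concerns what is estimated, not sample size.

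**What the arm contrast contains.** Let π be the difference between arms in the proportion who play sport, θ the effect of sport in SD, δ the effect of the package by any other route, and b the difference between regions that would exist anyway. Then, in a simple additive form:

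contrast = π × θ + δ + b

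In general this equals θ only if π = 1, δ = 0 and b = 0. Against the text:

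- π: no uptake rate is given for either arm. Participation is voluntary, so π = 1 is not credible.
- δ: the pedagogue works on club rules, trainers' skills and parental involvement. This can reach youngsters who would have played anyway. Hypothesis 6 treats club climate as a moderator, so the protocol's own model separates climate from participation.
- b: the design is a non-equivalent control group, as the article says.

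**Illustration (θ, π and δ are assumptions; b set to 0).**

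| Assumed situation | Contrast |
|---|---|
| θ = 0.40, δ = 0, π = 0.2 | 0.2 × 0.40 = 0.08 SD |
| θ = 0.40, δ = 0, π = 0.6 | 0.6 × 0.40 = 0.24 SD |
| θ = 0, δ = 0.10, any π | 0.10 SD |

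The third row, with no sport effect, gives a larger contrast than the first. Dividing the contrast by uptake does not repair this: in the third row it yields an apparent sport effect of 0.10 / 0.2 = 0.50 SD at π = 0.2, or 0.10 / 0.5 = 0.20 SD at π = 0.5.

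**The alternative: individual sport data.** Sport participation is measured at T0, T1 and T2, so hypotheses 1 to 3 can be examined directly, but only observationally. Simulations illustrate the limits. All inputs are assumed except three waves and 600 × 0.80 × 0.70 = 336 completers: 60% of outcome variance lies between persons, and sport has no true effect.

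- Players stably 0.34 SD better: a random-intercept model with undivided sport participation gives a coefficient of about 0.12 SD, significant in about 59% of runs. With a gap of 0.10 to 0.20 SD, it is significant in 10% to 27%.
- In the same setting, the within-person coefficient is about 0.00 and significant in about 5% of runs.
- With a time-varying common cause of sport and outcome added (0.10 SD per SD of the time-varying driver of sport), the within-person coefficient is about 0.175 SD and significant in about 77% of runs.

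A within-person term therefore removes stable differences between youngsters, but not circumstances that change together with sport.

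**The case against.** The strongest reply is that the authors already disclose most of this: baseline selection between arms, self-selection of joiners and dilution are all listed as limitations. That stands and narrows the point. But the limitations do not say that the arm contrast estimates the package effect, do not name the pedagogue as a separate route, and do not qualify the causal claim made in the same section.

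A second reply is that club climate belongs to the sport experience under study. That is a fair reading of the pedagogue's work. Even so, the exposure would be sport in a supported club after guidance by trained staff, which is not the exposure the hypotheses name.

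A third reply is that the analysis section commits to no faulty model. This also stands. A reader might infer that sport will enter a random-intercept model as a single undivided covariate, and so carry the self-selection. The data analysis section gives three nested levels, but names neither the exposure term nor a random-intercept-only structure. Such coding may properly be left to an analysis plan that is not shown.

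**Conclusion.** The point holds as a mismatch between the claimed effect and the comparison named to support it. Followed as written, the plan would state a causal conclusion about sport that the arm contrast does not support. This follows from the text alone and rests on no assumed figure. Its numerical size cannot be determined, because the article gives neither uptake by arm nor the strength of other routes; the table and simulations are illustrations only.

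Three stronger readings are not supported:

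- A reader might infer a required sport effect by converting f = 0.20 to a regional difference and dividing by uptake. The sample size section does not say which effect f describes, and the division assumes that everything runs through more sport, which contradicts the package argument.
- A reader might infer that hypotheses 1 to 3 cannot be addressed at all. They can, observationally, with the sport data collected at three times.
- A reader might infer that a within-person analysis would establish them causally. It removes only time-stable confounding.

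**What to change.** 1. Reword the sentence under Strengths and limitations and the planned aim 1 conclusion. The arm contrast at 6 and 18 months, in all youngsters by region whether or not they play sport, is the effect of the care-sport intervention, subject to the non-equivalent control group design.
2. Test hypotheses 1 to 3 in a separate analysis, using the sport participation items based on the Dutch guideline (RSO) at T0, T1 and T2. Adjust it for baseline and label it observational.
3. As a sensitivity analysis, split sport participation into each youngster's mean over the waves and the deviation from that mean. State that the within-person term removes only time-stable confounding.

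The cost is wording plus one derived split in the multilevel framework already planned; no new data are needed. The headline claim becomes more modest, and the within-person estimate is somewhat less precise. In the illustrative simulations its standard error was 0.064 against 0.056, and 0.092 against 0.068 when sport habits were very stable.

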### Implications for practice

The results from this study will be used to support stakeholders in the youth care and sport context in their effort to improve the personal development of socially vulnerable youth through sport participation. An intervention protocol will be developed for relevant stakeholders that seek to integrate sport activities in youth care practices. There is increasing attention in both politics and practice for the use of sport as an intervention for social problems. Findings from this study can support initiatives by providing insights on the social conditions and organisational factors of successful sport inclusion.

### Ethics approval

This study has been approved by the Medical Ethical Committee of Wageningen University (protocol number: NL47988.081.14**)** and has been registered with the Dutch Trial Register (NTR4621). Date of Registration: 2 June 2014.
